### 1. Study Title (including any abbreviated titles)

A pilot randomised cross-over trial of HoloLens2™ for the delivery of distributed medical care during COVID-19 in a simulated environment.

### 2. Date/Version

**Date:** 14/12/2020      **Version:** 4

### 3. Summary of Project

This pilot randomised cross-over study aims to assess the technical feasibility of a novel Mixed Reality (MR) headset known as the HoloLens 2™ (HL2) for the delivery of direct clinical care in simulated COVID-19 contaminated environments. The HL2 is an untethered holographic computer that is worn as a headset. Using software called 'Remote Assist' it permits a 'hands free' scalable telemedicine platform which can be used without the requirement for touch or interaction with a physical computer.

We will prospectively evaluate the impact of the device in the management of a simulated COVID-19 clinical resuscitation scenario. The study will be conducted according to a randomised cross-over design with participants completing two simulated clinical scenarios. Participants will be randomly assigned to one of two groups - standard care, or HL2 supported care – for the first scenario prior to cross-over. The primary outcome measure will be error rate as assessed by the validated ICECAP multi-dimensional error capture tool. Secondary outcomes pertaining to scenario completion, teamwork, PPE use, stress/cognitive load and user acceptability of the HL2 device will also be recorded. The study will be undertaken in a specialist clinical simulation facility facilitated by experienced simulation practitioners.

**6. Preferred Timetable**

**6a. Preferred Start Date:** 1st May 2021

**6b. Expected Date of Completion:** End of study definition is final participant visit

**7. Other Organisation(s) Involved and Funding**

**7a. Department/Organisation Requesting Research (if applicable):**  
Imperial College London

**7b. If you are receiving funding, please provide details here:** MOD Chief Scientific Advisor via Defence Science and Technology Laboratory (Dstl) and the Defence and Security Accelerator (DASA).

**7c. Please declare any competing or conflicts of interests:** None

**7d. Type of research**

i. **Equipment**

|  |
|--|
|  |
|--|

**8. Scientific Assessment Approval**

**8a. Name of SAC that has reviewed/approved this application:** Dstl SAC

**8b. Date of SAC approval:**

**8c. SAC reference number:** 1083/MODREC/20

**9. Purpose of the Study and Defence Benefit**

Telemedicine encompasses a wide range of technologies that support the delivery of remote care, and the use of such technologies has been identified as a key potential innovation in the response to COVID-19;(1) providing a means to efficiently deliver care and leverage access to multiple remote specialists whilst simultaneously protecting staff and patients from exposure to the virus.(2, 3) There is an opportunity for technology to not only bring additional benefits and scope to clinical care, but also to simultaneously act as personal protective equipment which may also act to reduce the risk of staff infection. During COVID-19 shortage of PPE has been a national emergency.(3) Protecting the health and safety of healthcare workers is vital to maintain the quality of care delivered to individual patients and the ability of health systems to deliver care at scale. In Italy up to 20% of healthcare workers became infected with the virus during the initial phase of the pandemic,(4) and a number of them died; a picture that is seen across the globe and in the UK. As such, there is a pressing need to reduce the risk of transmission of all pathogens transmitted from patients to healthcare workers via all practical means.

[figure not shown]

Figure 1. The HoloLens 2 Headset. It consists of a mounted computer (at rear of the head), a visor which projects holographic images on the user's eye. It also contains a forward-looking camera in the centre of the headset and sensors mounted at the front on each side. Finally, it possesses a noise cancelling microphone for voice communication.

HoloLens 2™ is an MR head-mounted device with a range of functionality (figure 1). The device is developed and marketed by Microsoft Corporation (Redmond, WA, USA). The headset combines several types of sensors (infra-red time-of-flight cameras, high definition RGB cameras, accelerometers and microphones), and provides a true heads-up display functionality with the ability to place 2D and 3D objects within a user's visual field, whilst also delivering live bidirectional communication via video. Mixed reality composites and voice can also be

[figure not shown]

Figure 2a  
HL2 wearer can visualise colleagues  
Situated remotely facilitating a bedside MDT

[figure not shown]

Figure 2b  
The wearer can also visualise imaging and  
electronic healthcare records 'heads up'.

shared with multiple remote users via the Remote Assist application (figure 2a and b). The HoloLens™ has been used in a variety of clinical scenarios including perioperative planning, surgical training and 3D telemedicine support.(5-7)

The HL2 system therefore has significant potential for defence benefit. Specifically:

- 1) Reduction of COVID-19 transmission risk and strengthening of staff safety by reducing need for team exposure to high-risk environments (figure 2a).
- 2) Improved heads-up situational awareness and data visualisation - electronic healthcare record and imaging data can be projected into the field of view, or objects virtually marked and illustrated in the real world by remote members of the clinical team (figure 2b). Moreover, data can be captured and streamed back to wider team by the end-user in the field, who also has the ability to virtually mark targets or objects of interest.

- 3) Support the provision of remote specialist access. Specifically, Remote Assist will aid the delivery of care by permitting multidisciplinary teams to function across wide geographical areas.
- 4) Deliver remote immersive education and training - all first-person views and MR content can be captured and securely streamed for educational and training use either in real-time or on-demand.
- 5) Generation of new knowledge and capabilities - the storage of all MR content captured through the device has the potential to create a rich repository of data from which future insights and technology developments can be leveraged through human or machine learning based analysis.

[figure not shown]

Figure 3: Adaption of standard PPE for use with the HL2 system. A strip of plastic has been removed at the front of the visor.

Despite this potential, the system has yet to be formally assessed in a structured manner and therefore the benefit of MR over standard clinical practice in clinical scenarios has yet to be fully assessed, and the true value proposition has yet to be defined. It is also still unclear how the lack of physical presence of a provider impacts the teamwork, communication, and workload of a clinical team e.g. during resuscitation.

The HoloLens2™ has been deployed to support the delivery of clinical care during COVID-19, and the early impact of its use has been reported by this research team as part of a quality improvement study at Imperial College London.(8) This demonstrated that it reduced the frequency of potential COVID-19 contacts by 80% during daily

clinical ward rounds because it reduced the number of team members that needed to enter a COVID-19 environment at any one time. This in-turn reduced PPE consumption rates. The benefit of the system was further improved because it can be controlled through the use of voice command or hand gestures which significantly reduces the need for physical contact with computer equipment and therefore the transmission of nosocomial infections. However, robust trial evidence is lacking and the exact mechanisms through which the system influences team performance are not defined. This is required before this technology can be deployed at scale within a military operational environment.

The HL2 system is a commercial device not designed for use in challenging or high- risk clinical environments. Therefore, in future it will be necessary to adapt standard PPE visors for use with the system. This is because the technology's sensors and cameras must be unimpeded by plastic (figure 3). Therefore, novel approaches are required that seamlessly allow the headset to be adopted when PPE is worn. These can be developed using a combination of 3D printed attachments for standard plastic visors. Whilst the commercial device is a relatively mature technology, further development work supported by this study such as the design of bespoke accessories to support compliance with infection prevention and control when working with aerosol generating procedures, and also further software development to support a more functional and user-centric clinical interface is required.

### **Work undertaken to support the delivery of this study:**

The study group is undertaking a technology development project to support the delivery of this study. The aim of this development stage is to establish the technical feasibility of using HoloLens™ with a 3D printed bespoke visor, and to develop and test standard processes for the secure collection and analysis of mixed reality outputs to support improvements in

technology deployment and clinical care. This work is being undertaken in two distinct work packages.

### *1 - Development of a bespoke 3D-printed face visor and linked accessories:*

We are creating a bespoke 3D printed face visor and linked accessories that permits the sensors and cameras of the HoloLens™ to continue to function whilst simultaneously providing adequate protection, particularly during AGPs in COVID-19 environments. An initial design phase with observations of clinical use of HoloLens™ headsets and interviews with frontline clinicians who may have to use the device in a range of clinical environments has been undertaken to define the ideal requirements for a future HoloLens™ protective visor and other relevant linked accessories such as light sources or additional audio equipment. This will inform the design and production of device specific protective equipment and accessories.

### *2 - Software development and inter-operability*

The MR content generated through the HoloLens™ has the potential to provide an enormously rich library of data that can inform better clinical practice, provide more effective medical education and support the development of new technologies. A key aim of this aspect of the supporting work is to provide a means to capture, store and annotate MR data captured during routine clinical interactions in a user-friendly method in order to curate a digital data repository that can support future clinical care, education and research.

## **10. Study Design, Method and Data Analysis**

## **Aims and objectives**

To prospectively assess the impact of HoloLens 2™ in a simulated COVID-19 setting for the assessment and resuscitation of critically unwell patients.

There are no secondary objectives for this study.

## **Hypothesis**

Remote care delivered with the HL2 is equivalent to standard clinical practice for team performance, workload and technical performance.

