#### Outcome measures:

The primary outcome will be

- Error rate as assessed by the validated ICECAP Tool (Imperial College Error Capture Tool) a validated multi-dimensional assessment of error

Secondary outcomes will be

- Time to complete the clinical scenario
- Successful completion of the clinical scenario - as assessed by simulation team
- Global assessment of team performance - assessed using the validated OTAS Tool (Observational Teamwork Assessment for Surgery) and T-SAW-C Tool (Teamwork Skills Assessment for Ward Care)
- Errors in PPE use - assessed according to Public Health England (PHE) guidance and number of visor failures (e.g., inadvertent removal, misting, contamination or obstruction of clinical care)
- Participant stress/cognitive load - assessed via the validated NASA Task Load Index (NASA-TLX) and State Trait Anxiety Index (STAI) Tools
- Usability / technology feedback questionnaire for those wearing the HL2

All questionnaire items and assessment tools listed above are provided in the attached documents. Participant responses will be collected at the time of study completion, and assessment of video recordings will be undertaken during the data analysis stage of the study

**Statistical analysis:** Standard descriptive data will be employed. Independent two-sample t-tests will be calculated for normal continuous data, including ICECAP and OTAS scores, and time-to completion data. The Wilcoxon-Mann-Whitney U test will be used to analyse TLX scores. Multivariate linear regressions will be calculated to control for potential confounders and to assess association. Within subject comparisons will also be made to assess how the technology influences individual performance.

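### The equivalence hypothesis covers team performance, workload and technical performance, but the only primary outcome (ICECAP error rate) is not named in it and covers at most one of the three

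*Protocol*

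**What the plan says.** The Protocol, section 10 (Hypothesis), makes one claim: "Remote care delivered with the HL2 is equivalent to standard clinical practice for team performance, workload and technical performance". Project Design, in the same section, treats this as the study's central hypothesis.

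Section 3 names one primary outcome: "The primary outcome measure will be error rate as assessed by the validated ICECAP multi-dimensional error capture tool". Section 10 (Outcome measures) repeats it: "Error rate as assessed by the validated ICECAP Tool (Imperial College Error Capture Tool) a validated multi-dimensional assessment of error".

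Two of the hypothesis's domains appear only in the list of secondary outcomes:
- Team performance: "Global assessment of team performance - assessed using the validated OTAS Tool (Observational Teamwork Assessment for Surgery) and T-SAW-C Tool".
- Workload: "Participant stress/cognitive load - assessed via the validated NASA Task Load Index (NASA-TLX) and State Trait Anxiety Index (STAI) Tools".

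Section 10 (Aims and objectives) adds: "There are no secondary objectives for this study".

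The statistical analysis paragraph plans independent t-tests for ICECAP, OTAS and completion time, a Wilcoxon-Mann-Whitney test for TLX, regressions and within-subject comparisons. The protocol gives no equivalence margin. Section 13e says that no power calculation was possible and that the pilot is meant to inform one for a later trial.

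**The concern.** A hypothesis, an objective and a primary outcome should describe the same question. Here the hypothesis asks about three domains and the primary outcome answers at most one. A reader of the results would not know whether the hypothesis stands or falls on the ICECAP error rate or on all three domains together.

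What is at stake is the conclusion. As written, a report could state that HL2 care is equivalent for teamwork and workload when that rests on secondary outcomes, compared by tests of difference, in 30 people. There is also a consequence for the later trial. Section 13e ties the power calculation to the standard deviation of the primary outcome, so that trial would be sized on a measure that the hypothesis leaves out.

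Aligning these three elements belongs in the protocol. It is not a detail that a statistical analysis plan would normally settle.

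**Working it through.** **1. Hypothesis against outcomes**

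| Domain in the hypothesis | Measure in section 10 | Status |
|---|---|---|
| Team performance | OTAS, T-SAW-C | Secondary only |
| Workload | NASA-TLX, with STAI | Secondary only |
| Technical performance | None assigned; candidates are ICECAP error rate, time, scenario completion and PPE errors | Primary only if ICECAP is meant |

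Scenario completion shows why the third row is open. It is listed as "Successful completion of the clinical scenario - as assessed by simulation team" and could be read as technical performance just as well as an error count. On the reading most favourable to the plan, the primary outcome covers one domain of three.

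**2. Can the primary outcome decide the hypothesis?** Two possible results:
- *ICECAP errors equal, TLX workload higher with HL2.* The primary shows no difference, but the hypothesis is contradicted on workload.
- *ICECAP errors differ, teamwork and workload alike.* The hypothesis fails if ICECAP stands for technical performance. If it does not, the primary outcome says nothing about the hypothesis. The protocol does not say which applies.

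**3. Could 30 participants support the equivalence claim?** The protocol gives no SD, margin, alpha or power, so there is no figure of its own to reproduce. Assumptions: true difference zero, one-sided 5% in each of two one-sided tests, 80% power, normal approximation, and within-person correlation r from 0 to 0.7. The number of participants, 30 in each condition, is from section 10.

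Standard error in SD units: SE = √(2(1 − r)/30).

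Smallest margin for one outcome: SE × (1.645 + 1.282) = SE × 2.926.

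For all three domains together, taken as independent, each needs power 0.80^(1/3) = 0.928. The multiplier becomes 1.645 + 1.801 = 3.446.

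| r | SE | Margin, one outcome | Margin, all three |
|---|---|---|---|
| 0 | 0.258 | 0.76 SD | 0.89 SD |
| 0.3 | 0.216 | 0.63 SD | 0.74 SD |
| 0.5 | 0.183 | 0.53 SD | 0.63 SD |
| 0.7 | 0.141 | 0.41 SD | 0.49 SD |

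**4. Would a non-significant t-test do instead?** Take a true difference of 0.5 SD, the independent t-test and an assumed two-sided 5% level. The mean of the test statistic is 0.5/0.258 = 1.94 against a critical value of 1.96, so power is Φ(1.94 − 1.96) ≈ 49%. A difference of half an SD would be missed about half the time. Non-significance therefore does not support equivalence.

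**The case against.** The best defence has four parts.

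*One primary outcome is named, consistently.* Sections 3 and 10 agree, there are two conditions, and calling one outcome primary is itself a ranking. This stands. A reader might infer that no comparison decides the trial, but the documents do not support that. The gap is narrower: the comparison that is named does not decide the hypothesis that is stated.

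*Testing several domains does not by itself inflate error.* A reader might infer an uncontrolled family of tests. The hypothesis joins its domains with *and*. If each must show equivalence against a margin, the chance of a false claim stays at or below the level of a single test without adjustment, and the price is power. With tests of difference, one could argue that a significant result in any domain counts against the hypothesis, so that false alarms add up. But a significant difference can still lie inside a margin. Moreover, the planned independent t-tests ignore the pairing and are conservative if a participant's two results correlate positively. At an assumed r = 0.3 the true size is 2 × [1 − Φ(1.96/√0.7)] ≈ 1.9% per test, and 1 − (1 − 0.019)³ ≈ 5.6% for three independent outcomes. The within-subject comparisons would not be conservative in this way. Multiplicity rules for secondary outcomes may also sit in an analysis plan that is not shown. The multiplicity charge is therefore not made.

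*It is a pilot.* This stands and lowers the severity. It does not remove the mismatch, because the hypothesis is worded as a claim of equivalence rather than as an aim to estimate.

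*One broad objective can be served by several outcomes.* This is also true. The absence of secondary objectives is not a contradiction by itself, but it leaves teamwork and workload with no stated lesser role.

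**Conclusion.** The point holds as a misalignment in the protocol's own text. The hypothesis asserts equivalence in three domains. The primary outcome is absent from its wording and covers at most one of them, and the other two rest on secondary outcomes only. This conclusion needs no numerical assumption.

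The figures show only that the equivalence claim is out of reach for all but wide margins: about 0.76 to 0.41 SD for one outcome and 0.89 to 0.49 SD for all three, for r from 0 to 0.7. They rest on the assumed error rates, a true difference of zero and, for the joint figure, independent domains.

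Severity is minor to moderate, and the correction is a cheap improvement.

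**What to change.** 1. **Hypothesis (section 10).** Restate it on the primary outcome and say openly what becomes of the equivalence claim. For example: *The study will estimate the difference in ICECAP error rate between HL2-supported and standard care, with a 95% confidence interval. As a pilot without a power calculation, it makes no claim of equivalence.* If the sponsor wishes to keep the word *equivalent*, the protocol should state a margin for the ICECAP error rate.
2. **Outcome measures (section 10).** State that team performance, workload and the other secondary outcomes will be reported as estimates with 95% confidence intervals and without a claim of equivalence.
3. **Aims and objectives (section 10).** Replace the statement that there are no secondary objectives with a short list that matches those outcomes.

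The cost is wording in three places, with no new data, staff or participants. The downside is that the sponsor gives up an equivalence claim for teamwork and workload, which 30 participants without a power calculation cannot support. The intervals remain useful for planning: by the standard errors above, a paired 95% interval would have a half-width of about 1.96 × SE, that is 0.42 SD at r = 0.3 and 0.28 SD at r = 0.7.

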## **PROJECT DESIGN**

Because the evolution of the COVID-19 pandemic is unpredictable we will utilise a simulated environment to establishing our core hypothesis about the effectiveness of MR telemedicine.

This is a prospective observational simulated trial designed to evaluate the impact of MR telemedicine technology (HL2) on care delivered during a simulated adult resuscitation.

**Recruitment:** Study participants will be recruited from a convenience sample of clinical staff who provide care to COVID-19 patients at Imperial College Healthcare NHS Trust and Imperial College London. This will include doctors in training and equivalent non-training medical staff, in addition to independent specialist nurse practitioners. All participants will have prior experience/qualifications in advanced life support skills and resuscitation. Informed consent will be obtained prior to commencing the study.

**Quality assurance and standardisation:** All team members will receive standardised training in two components of practice prior to entry into the study in order to familiarise themselves with the HL2 device and ensure basic technical competency:

1. HL2 operation: All participants will receive a standardised tutorial on how to operate the HL2 headset. This 15-minute practical induction will provide them fundamentals of use, namely a) how to wear PPE with the device b) how to turn on the device, access software and interact with the device c) how to make and receive calls and use clinical data. The training will be run as a hands-on demonstration/run-through clinical scenario provided by the study team in which participants will be able to familiarise themselves with the HL2 device and its use. All participants will be expected to perform a simple competency test before being allowed to proceed to the trial phase to ensure standardised basic technical competency and mitigate device related 'first-use' learning effects.

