### 13. Participants

**13a. Number of Participants:** 30

**13b. Lower Age Limit:** 18

**13c. Upper Age Limit:** No restrictions

**13d. Birth Sex (male/female):** No restrictions.

**13e. Please provide justification for the sample size, and age/sex restrictions:** It is not possible to perform a power calculation for this work, as there are currently no data available on HL2 interventions upon which a standard deviation of the primary outcome measure can be calculated. The objective of this pilot study is therefore to determine a power calculation for a formal randomised control trial in patients.

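### The protocol sets out to establish equivalence, but the tests it names can only look for a difference and cannot support that hypothesis

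*Protocol*

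**What the plan says.** The Hypothesis paragraph of protocol section 10 states a single claim, covering three domains: "Remote care delivered with the HL2 is equivalent to standard clinical practice for team performance, workload and technical performance". The Project Design paragraph that follows says what the study is for: "we will utilise a simulated environment to establishing our core hypothesis about the effectiveness of MR telemedicine".

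The statistical analysis paragraph, under Outcome measures in the same section, fixes the methods:

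- ICECAP (the primary outcome), OTAS and time: "Independent two-sample t-tests will be calculated for normal continuous data, including ICECAP and OTAS scores, and time-to completion data".
- Workload: "The Wilcoxon-Mann-Whitney U test will be used to analyse TLX scores".
- Regression: "Multivariate linear regressions will be calculated to control for potential confounders and to assess association".
- Within-person analysis, with no method named: "Within subject comparisons will also be made to assess how the technology influences individual performance".

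The protocol contains no margin, no confidence-interval criterion and no other rule for concluding equivalence.

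On the number of participants, section 13e says "It is not possible to perform a power calculation for this work, as there are currently no data available on HL2 interventions". It goes on to give the pilot's objective as providing the power calculation for a later randomised trial in patients.

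**The concern.** A t-test or a Mann-Whitney test starts from no difference and can only reject it. Rejection would count against the hypothesis of equivalence. Failure to reject does not count for it, because a small or noisy study fails to reject whether or not a real difference exists. So neither outcome of the named tests can support the claim the study is meant to establish.

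Non-significance is the only result of these tests that could be taken as favouring the hypothesis, and it becomes more likely as the trial becomes less precise. The primary outcome is the error rate in a simulated resuscitation, and section 9 says firmer trial evidence is needed before the device is deployed at scale in military operations. A mistaken reading of equivalence could hide added errors at that step.

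There is a second conflict. Establishing equivalence is a confirmatory aim; providing inputs for a later power calculation, as in section 13e, is an estimation aim. The protocol gives both and does not reconcile them.

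**Working it through.** **Is there a figure to reproduce?** No. The protocol gives N = 30 without alpha, power, SD, effect size or margin, and says no power calculation was possible.

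**Inputs.** From the protocol (section 10): 30 participants, each completing one scenario per condition, so 30 observations per condition. Assumed, because the protocol gives none: two-sided alpha 0.05 for difference tests; two one-sided 5% tests (equivalently a 90% CI) for equivalence; normal outcomes with equal SD; within-person correlation ρ from 0 to 0.7; no dropout; no period or scenario effect.

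**1. How often would the named t-test miss a real difference?** The test reaches significance when the observed difference exceeds about t(0.975, 58) × √(2/30) = 2.002 × 0.258 = 0.52 SD. In cross-over data the true standard error of the difference is SD × √(2(1−ρ)/30), which the unpaired test ignores. Simulated proportion of trials with a non-significant result:

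| True difference | ρ = 0 | ρ = 0.3 | ρ = 0.5 | ρ = 0.7 |
|---|---|---|---|---|
| 0.5 SD | 52% | 53% | 53% | 54% |
| 0.3 SD | 79% | 83% | 87% | 92% |

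A paired t-test also leaves many non-significant results. From the noncentral t distribution, as 1 − power at ρ = 0.3, 0.5 and 0.7:

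- 0.5 SD: 39.1%, 24.6% and 7.3%.
- 0.3 SD: 73.1%, 64.5% and 46.4%.

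The gap between the unpaired and paired figures comes from ignoring the pairing. That is a separate defect and is not evidence on equivalence versus difference.

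**2. What could a real equivalence test show with 30 people?** Let SD_d be the SD of the paired difference. The 90% CI half-width is t(0.95, 29)/√30 = 1.699/5.477 = 0.31 SD_d. With a true difference of 0, the simulated power of two one-sided 5% tests is:

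| Margin (in SD_d) | 0.3 | 0.4 | 0.5 | 0.6 |
|---|---|---|---|---|
| Power | 5% | 38% | 70% | 88% |

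Power reaches 80% at a margin of 0.548 SD_d. As a check, the normal approximation gives (z0.95 + z0.90)/√30 = (1.645 + 1.282)/5.477 = 0.534; using t in place of z accounts for the remainder.

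**3. The same margin in units of the outcome SD.** SD_d = SD × √(2(1−ρ)), so the margin needed for 80% power is:

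- ρ = 0.3: 0.548 × 1.183 = 0.65 SD
- ρ = 0.5: 0.548 × 1.000 = 0.55 SD
- ρ = 0.7: 0.548 × 0.775 = 0.42 SD

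Put the other way, at a margin of 0.5 outcome SD the paired equivalence test has power of about 46%, 70% or 93% at these three correlations.

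**The case against.** Several points on the other side are fair.

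- **It is a pilot.** The title and summary call it one, the summary speaks of technical feasibility, the aim is worded neutrally as assessing impact, and section 13e looks ahead to a later trial. On those passages estimation is already most of the purpose. This stands, and it supports the preferred fix. It does not remove the Hypothesis paragraph or the statement in Project Design that the study is to establish that hypothesis.
- **A margin and a confidence-interval criterion could be in the SAP.** True, and their absence from the protocol would not be a finding alone. But the protocol itself pairs an equivalence hypothesis with difference tests, including for the primary outcome. A SAP that tested equivalence would depart from the tests the protocol names, so the protocol needs correcting either way.
- **Difference tests are not the whole plan.** Descriptive statistics, regression and within-subject comparisons are also planned, and these could give an estimate and an interval. So it would be wrong to say that only difference tests are planned. None of them is tied to an equivalence criterion, so the mismatch remains.
- **Nobody says non-significance will be called equivalence.** A reader might infer that the team intends to conclude equivalence from p > 0.05. The protocol states no such rule, nor any alpha. Only the weaker statement holds: the wording leaves that misreading open.
- **The percentages rest on assumptions.** Correlation, SD and margin are all unknown, which is why ranges are shown. The logical mismatch does not depend on them.

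**Conclusion.** The point holds as a contradiction within the protocol: the stated hypothesis is equivalence, the named tests can only reject equality, and the remaining analyses carry no criterion for equivalence. It also conflicts with the estimation purpose in section 13e.

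On the stated assumptions, the named t-test would be non-significant in roughly half of trials with a true 0.5 SD difference and in about four-fifths or more at 0.3 SD, so non-significance says little about equivalence. A properly built paired equivalence test on 30 people would have 80% power only for a margin of about 0.42 to 0.65 outcome SD (ρ from 0.7 down to 0.3), and that assumes the true difference is exactly zero. Whether such a margin is tolerable in ICECAP errors cannot be judged from the protocol. The documents do not support going further and saying that the investigators plan to report a non-significant result as equivalence.

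**What to change.** **Preferred: estimation.** Reword the Hypothesis paragraph, and the matching sentence in Project Design, along these lines: *The study will estimate the mean within-participant difference in ICECAP errors (HL2 minus standard care) with its 95% confidence interval, and the standard deviation needed to plan a later trial. A non-significant test will not be taken as evidence of equivalence.* This agrees with section 13e and leaves N at 30.

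**Alternative: keep equivalence for ICECAP.** Fix and justify a margin in error units before the first participant. Claim equivalence only if the paired 90% CI lies wholly inside the margin, and otherwise report the result as inconclusive. Any other domain for which equivalence is claimed needs its own margin, or is reported descriptively.

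**Cost.** The preferred route changes wording only. The alternative also requires agreeing a margin, but no extra participants as such. The price in both cases is a more modest claim: with 30 people only a wide margin can be met unless within-person correlation is high.
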